## 9.9. Clinical trial schedule

### 9.9.1. Screening visit

- Screening tests for the test subjects who have agreed in writing to participate in the clinical trial to review the suitability are performed on an empty stomach for at least 8 hours within 7 days (-7d) from the first intervention date (1 week), excluding those with clinically significant abnormalities by the following tests. For reference, if the abnormal findings in the screening test item are judged to be a temporary change, the suitability may be

Version 2.6

reexamined through a re-examination before the first intervention date.

- Demographics and medical examination
- Vital signs and physical examination
- Clinical laboratory examination (hematologic test / biochemical test / urinalysis / immunology test / blood clotting test / serological examination)
- 12-lead ECG
- Salivary flow rate (SFR) test
- Evaluation of visual analog scale (VAS) for xerostomia

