| Primary and secondary outcomes | 
1. Primary outcome
 
 
- Unstimulated SFR after 12 weeks of treatment
 
- Participants will abstain from food intake for at least one hour. The participants will need to rinse their mouth with water, held it open, and gather saliva for 5 min. SFR (ml/min) is calculated by dividing the measured amount of saliva (ml) by time (5 min).
 
 
2. Secondary outcomes
 
 
- Stimulated SFR after 12 weeks of medication
 
- Differences and mean percentage changes in unstimulated and stimulated SFR from baseline (week 0) to the end of the trial (week 12)
 
- To determine the stimulated SFR, the participants will be encouraged to suck sugar-free lemon candy. The procedure for measuring the stimulated salivary flow is the same as that for measuring the unstimulated salivary flow.
 
- Differences and mean percentage change in the visual analogue scale (VAS) and 14-item Oral Health Impact Profile (OHIP-14), and from baseline
 
 |

|                     |                                                                                                                                                                                                                                                                                                                                                                                                                                                                                                                                                                                                                                                                                                                                                                                                                                                                                                                                                                                                                                                                                                                                                                                                                                                                                                                                                                                                                   |

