### **10.1.5. Salivary flow rate (SFR) test**

- Measuring by collecting saliva in both unstimulated and stimulated state
- (Unstimulated) The participants will abstain from food intake for at least one hour, and they will need to rinse their mouth with water, held it open, and gather saliva for 5 min.
- (Stimulated) The participants will be encouraged to suck sugar-free lemon candy. The procedure for measuring the stimulated salivary flow is the same as that for measuring the unstimulated salivary flow.

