## **10.2. Evaluation of efficacy**

### **10.2.1. Salivary flow rate (SFR) test**

- Visit 2 (Week 0) is replaced by screening test.
- Evaluation at Visit 3 (Week 4), Visit 4 (Week 8), Visit 5 (Week 12).

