### **13.3.2. Secondary outcomes efficacy assessment**

#### **13.3.2.1. Evaluation items**

- Stimulated SFR after 12 weeks of medication
- Differences and mean percentage changes in unstimulated and stimulated SFR from baseline (week 0) to the end of the trial (week 12)
- Differences and mean percentage change in the visual analogue scale (VAS) and 14-item Oral Health Impact Profile (OHIP-14), and from baseline (week 0) to the end of the trial (week 12).
- Differences and mean percentage changes in the uptake ratio (UR), maximum accumulation (MA), and maximum secretion (MS) on salivary scintigraphy from baseline (week 0) to the end of the trial (week 12).

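### The food interval before the screening salivary flow test, which is the week-0 baseline, is set at 8 hours in one section and one hour in another; follow-up visits need only one hour

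*Protocol*

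**What the plan says.** Section 9.9.1 states that the screening tests "are performed on an empty stomach for at least 8 hours within 7 days (-7d) from the first intervention date". The list beneath includes "Salivary flow rate (SFR) test", and nothing restricts the fast to the blood samples.

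Section 10.1.5, which falls under the heading for screening evaluation items, gives the collection procedure for the same test: "The participants will abstain from food intake for at least one hour, and they will need to rinse their mouth with water". The outcome definition in the protocol summary repeats it: "Participants will abstain from food intake for at least one hour".

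For efficacy, 10.2.1 says of the SFR that "Visit 2 (Week 0) is replaced by screening test", followed by "Evaluation at Visit 3 (Week 4), Visit 4 (Week 8), Visit 5 (Week 12". It adds no food rule for those visits. Both schedule tables agree: SFR is marked at Visit 1 and not at Visit 2.

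The baseline value is then used in 13.3.2.1, where a secondary outcome is "Differences and mean percentage changes in unstimulated and stimulated SFR from baseline (week 0) to the end of the trial (week 12". Section 13.3.2.2 plans paired t or Wilcoxon signed-rank tests within each group. The primary outcome in 13.3.1 is the week-12 unstimulated SFR compared between groups; its definition uses no baseline value.

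**The concern.** The same reading is given two different pre-collection conditions, and that reading does two jobs. It is the starting point for every change and percentage change in SFR, and it decides entry: at or below 0.25 mL/min for everyone, and at or below 0.1 mL/min for those qualifying through Sjogren's syndrome.

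An 8-hour fast satisfies both screening rules, so full compliance means a baseline after 8 hours or more. Full compliance at weeks 4, 8 and 12 needs only one hour. If flow differs between a long and a short fast, part of any within-arm change reflects the measuring condition and not the treatment. If the four centres resolve the contradiction differently, the baseline is also not the same measurement across centres.

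**Working it through.** **1. The rules side by side**

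| SFR reading | Rule | Where |
|---|---|---|
| Screening (= week 0) | at least 8 hours | 9.9.1 |
| Screening (= week 0) | at least 1 hour | 10.1.5 |
| Weeks 4, 8, 12 | at least 1 hour; no 8-hour rule | outcome definition in the summary; 9.9.2 and 10.2.1 add no food rule |

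The shortest fast meeting both screening rules is max(8, 1) = 8 hours. The shortest meeting the follow-up rule is 1 hour. The text therefore allows a mismatch but does not force one, since all the rules are minimums.

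Two other places leave the baseline loose. The note under the summary schedule accepts results from the same hospital up to 30 days old as screening results, and states no fasting condition. Section 9.9.2 lists an SFR test at Visit 2, which 10.2.1 replaces by the screening value.

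**2. The plan's own figure.** The sample size has n per arm = 2σ²(Zα + Zβ)²/d², with σ = 0.35, d = 0.21, one-sided α = 0.05 and power 90%. This gives 48, and 48/(1 - 0.20) = 60, as stated. Nothing in it depends on the fasting rule.

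**3. What a shift would touch.** The documents give no fasting effect, so one is assumed. Let true baseline be 0.15 mL/min (assumed), week-12 means 0.38 for control (the figure the protocol cites for 5 mg pilocarpine) and 0.30 for experimental (assumed). Let s be a baseline shift common to both arms. Then:

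- change = week 12 - (0.15 + s)
- percentage change = 100 × change / (0.15 + s), computed on group means
- between-arm difference in change = 0.30 - 0.38 = -0.08, with no s in it
- between-arm difference in percentage change = 100 × (0.30 - 0.38)/(0.15 + s)

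| s (mL/min) | Change, control | Change, experimental | Difference in change | Difference in % change (points) |
|---|---|---|---|---|
| -0.05 | 0.28 | 0.20 | -0.08 | -80 |
| -0.02 | 0.25 | 0.17 | -0.08 | -62 |
| 0 | 0.23 | 0.15 | -0.08 | -53 |
| +0.02 | 0.21 | 0.13 | -0.08 | -47 |
| +0.05 | 0.18 | 0.10 | -0.08 | -40 |

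Within-arm change moves one for one with s. The between-arm percentage difference keeps its sign but changes size, because baseline is its denominator. The between-arm absolute change and the week-12 comparison do not move.

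**4. Sensitivity of the paired test.** Assumptions: log-normal flow with mean 0.17 and SD 0.13 (the cited placebo figures), within-person CV 30% to 40% (not in the documents), 48 per arm and no drug effect. Share of simulated trials with a paired t-test at p < 0.05:

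| Follow-up flow relative to baseline condition | Share positive |
|---|---|
| 20% lower | 64-85% |
| 10% lower | 19-31% |
| equal | about 5% |
| 10% higher | 17-26% |
| 20% higher | 49-69% |
| 30% higher | 80-94% |

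These rates follow from the assumed shift. They show how sensitive the test would be, and they are not evidence that a shift exists. This distribution also puts about 18% of baseline readings above 0.25 mL/min, which entry excludes, so the table is a rough guide only.

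**The case against.** The best counter-argument is that the test-specific rule should govern. Section 10.1.5 describes how the screening SFR is collected and says one hour, the outcome definition says the same, and on that reading conditions match at every visit. The 8-hour phrase in 9.9.1 heads a list that also contains demographics, ECG and VAS, so it looks like a visit-level instruction. The screening chemistry includes glucose, triglyceride, HDL and LDL, a plausible reason for a fast. Follow-up readings may also be taken after a long fast.

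This stands to the extent that a reader cannot call the 8-hour baseline settled. It does not remove the contradiction. The SFR test is on the 9.9.1 list without exemption, and no text says which section prevails.

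Four stronger readings are tempting, and the documents do not support them:

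- *That SFR will change from baseline even without a drug effect.* The documents do not establish that a fasting effect exists, which way it goes, or how large it is.
- *That the shift can be judged against the 0.21 mL/min margin.* The margin applies to the between-arm week-12 difference, where a baseline shift does not enter.
- *That baseline becomes a weaker covariate.* Multiplying one set of readings by a constant leaves their correlation with the other unchanged, and the protocol plans ANCOVA for the primary outcome only if baselines differ significantly.
- *That the treatment comparison is biased.* Screening SFR precedes treatment and follows the same text in both randomised arms, so a common shift cancels in absolute change.

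It is also fair that within-arm tests, with entry capped at 0.25 mL/min and no placebo arm, are already open to regression to the mean and could not carry a treatment claim alone. That limits the harm here, but the tests are planned and will be reported.

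**Conclusion.** The point holds as an unresolved contradiction about how the baseline SFR is collected, together with follow-up visits whose stated minimum is shorter than one of the two baseline rules. Within-arm change in unstimulated and stimulated SFR, the paired tests, percentage change and eligibility at the two flow thresholds are exposed. The primary non-inferiority comparison, the between-arm absolute change and the sample size are not.

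The size cannot be stated from the documents. The illustrations rest on an assumed shift, an assumed baseline and an assumed within-person CV. They show only that a modest shift in either direction would matter to the paired tests. That the between-arm absolute change is unaffected rests on randomisation and on both arms being measured under the same rule at each visit. This is a minor to moderate point on secondary outcomes.

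**What to change.** Choose one pre-collection food interval for the SFR test, and preferably one time of day, and apply it at screening and at Visits 3 to 5. One way is to limit the 8-hour fast in 9.9.1 to the blood tests and state the SFR interval once, in 10.1.5, with 10.2.1 and the summary referring to it. While doing so, align the Visit 2 SFR entry in 9.9.2 with 10.2.1, and say whether an earlier result accepted under the 30-day note must meet the same SFR condition.

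The cost is protocol wording and somewhat less freedom in scheduling visits. No extra test is needed. For participants already measured, the food interval before the screening SFR, where it was recorded, would show whether the two conditions differed in practice.

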#### **9.9.2. Visit 2~5 (Week 0~12)**

- Eligible participants are randomly allocated to either the experimental or control group after screening based on the inclusion and exclusion criteria and written informed consent.
- Both experimental and control groups receive 4-week clinical trial drugs every 4 weeks (Before administration (0 weeks, Visit 2), 4 weeks after administration (4 weeks  $\pm$  2 days, Visit 3), and 8 weeks after administration (8 weeks  $\pm$  2 days, Visit 4)).
- The following tests will be conducted at each visit, including before administration (0 weeks, Visit 2), 4 weeks after administration (4 weeks  $\pm$  2 days, Visit 3), 8 weeks after administration (8 weeks  $\pm$  2 days, Visit 4), and 12 weeks after administration (12 weeks  $\pm$  2 days, Visit 5).
  - Assessment of drug compliance and return of unused clinical trial drugs
  - Monitoring adverse events and evaluating concomitant medication
  - Vital signs and physical examination
  - Clinical laboratory examination (hematologic test / biochemical test / urinalysis)
  - Salivary flow rate (SFR) test
  - Evaluation of visual analog scale (VAS) for xerostomia

Version 2.6

- Salivary scintigraphy
- 14-item Oral Health Impact Profile (OHIP-14) questionnaire
- 5-level EuroQol 5-dimensional (EQ-5D-5L) questionnaire

#### **9.10. First aid medicine**

- No additional first aid medication

#### **9.11. Prohibited drug in combination**

Coumadin, heparin, warfarin, aspirin, anticholinergics, first-generation antihistamines, antidepressants with anticholinergic effects, monoamine oxidase inhibitors, diuretics, mineralocorticoids,  $\beta$ -adrenaline antagonist, or digitalis. Patients taking low-dose aspirin or  $\beta$ -adrenaline antagonist can participate in the protocol based on the cardiologist's opinion.

#### **9.12. Permitted drug in combination**

- Drugs other than prohibited drugs in combination are allowed, but they are reviewed by principal investigator and sub-investigators during screening and clinical trials period.

### **10. Observation items and clinical examination items**

#### **10.1. Screening evaluation items**

- Evaluate and inspect the following items to select the test subjects suitable for participation in clinical trials based on the inclusion and exclusion criteria.

##### **10.1.1. Evaluation of general items**

- Gender, age
- Past medical history, recent medical history, and drug use history
- Information on smoking and alcohol intake

Version 2.6

- History of head and neck surgery and radiotherapy

#### **10.1.2. Vital signs, physical examination**

- Blood pressure, pulse rate (measured with no sudden change in position for more than 3 minutes), and respiratory rate
- Body temperature (tympanic)
- Height (cm), Weight (kg)

#### **10.1.3. 12-lead ECG**

- Record the ventricular rate (beats/min), PR interval (msec), QRS (msec), QT/QTc (msec) from the automatic analysis & recording.

#### **10.1.4. Clinical laboratory examination**

##### **10.1.4.1. Hematology test**

- WBC with differential count (segmented neutrophil, lymphocyte, monocyte, eosinophil, basophil), RBC, hemoglobin, hematocrit, platelet

##### **10.1.4.2. Biochemical test**

- glucose, BUN, uric acid, cholesterol, total protein, albumin, total bilirubin, alkaline phosphatase, AST, ALT,  $\gamma$ -GTP, CPK, LDH, creatinine, sodium, potassium, chloride, triglyceride, HDL, LDL, C-reactive protein, phosphorus, calcium

##### **10.1.4.3. Urinalysis**

- pH, specific gravity, protein, bilirubin, glucose, urobilinogen, ketone, nitrite, blood, leukocyte, microscopy (Urine RBC, Urine WBC, Urine Epithelial Cell, others)

##### **10.1.4.4. Immunology test**

Version 2.6

- ANA, Anti-Ro/SSA, Anti-La/SSB

#### **10.1.4.5. Blood clotting test**

- PT, aPTT

#### **10.1.4.6. Serological examination**

- HBsAg, anti-HBs Ab, anti-HCV Ab, IgM anti-HAV Ab

### **10.1.5. Salivary flow rate (SFR) test**

- Measuring by collecting saliva in both unstimulated and stimulated state
- (Unstimulated) The participants will abstain from food intake for at least one hour, and they will need to rinse their mouth with water, held it open, and gather saliva for 5 min.
- (Stimulated) The participants will be encouraged to suck sugar-free lemon candy. The procedure for measuring the stimulated salivary flow is the same as that for measuring the unstimulated salivary flow.

### **10.1.6. Evaluation of visual analog scale (VAS) for xerostomia**

- Evaluate xerostomia-related symptoms.
- The degree of symptoms is assessed using the VAS (a numerical measure of current pain with '0' no discomfort and '10' intolerable very severe discomfort).

## **10.2. Evaluation of efficacy**

### **10.2.1. Salivary flow rate (SFR) test**

- Visit 2 (Week 0) is replaced by screening test.
- Evaluation at Visit 3 (Week 4), Visit 4 (Week 8), Visit 5 (Week 12).

### **10.2.2. Evaluation of VAS for xerostomia**

## Version 2.6

- Visit 2 (Week 0) is replaced by screening test.
- Evaluation at Visit 3 (Week 4), Visit 4 (Week 8), Visit 5 (Week 12).

**10.2.3. Salivary scintigraphy**

- Evaluation at Visit 2 (Week 0) and Visit 5 (Week 12).
- For the objective evaluation of salivary gland function, salivary scintigraphy will be performed after the administration of a radiotracer (Technium-99m pertechnetate).
- After intravenous administration of Tc 99m sodium pertechnetate 370 MBq to patients, images are obtained using a low energy-high sensitivity collimator-type dual-head gamma camera (Philips Forte, Philips Medical Systems).
- Images are obtained 5 min, 15 min, and 30 min after intravenous administration of radiotracer, and front images are obtained in the same way after administration of salivary gland secretion stimulators (lemon candy).
- During the examination, the patient's head is fixed and instructed not to swallow saliva.
- To analyze the scintigraphy images, the counts of the regions of interest (ROI) will be evaluated in the parotid and submandibular glands. Three parameters – uptake ratio (UR), maximum accumulation (MA), and maximum secretion (MS)– will be calculated using the following formulas
- (1) UR is calculated as the salivary gland count – the background count.
- (2) The MA (%) is calculated as follows: (maximum activity before stimulation – initial activity 5 min after radiotracer injection) × 100 / maximum activity before stimulation.
- (3) The MS (%) is calculated as (maximum activity prior to stimulation – activity after stimulation) × 100 / peak activity before stimulation.

**10.2.4. OHIP-14 (The 14-item Oral Health Impact Profile) Questionnaire**

## Version 2.6

- Evaluation at Visit 2 (Week 0), Visit 3 (Week 4), Visit 4 (Week 8), and Visit 5 (Week 12).
- Subjective quality of life will be evaluated using OHIP-14 Korean version. The responses will be measured on a scale ranging from 0 (never) to 4 (always), generating a total score of 0 to 56 (lowest quality).

| How often do the following situations occur due to a disease in your mouth? |            |             |                   |                 |             |
|-----------------------------------------------------------------------------|------------|-------------|-------------------|-----------------|-------------|
|                                                                             | 0
Never | 1
Rarely | 2
Occasionally | 3
Frequently | 4
Always |
| Problems with pronunciation                                                 |            |             |                   |                 |             |
| Bad sense of taste                                                          |            |             |                   |                 |             |
| Pain                                                                        |            |             |                   |                 |             |
| Discomfort when eating                                                      |            |             |                   |                 |             |
| Concern for the mouth                                                       |            |             |                   |                 |             |
| Self-consciousness due to oral problems                                     |            |             |                   |                 |             |
| Dissatisfaction with food intake                                            |            |             |                   |                 |             |
| Interruption of meals                                                       |            |             |                   |                 |             |
| Difficulty relaxing due to oral problems                                    |            |             |                   |                 |             |
| Embarrassment arising from oral problems                                    |            |             |                   |                 |             |
| Irritability                                                                |            |             |                   |                 |             |
| Problems at work due to oral problems                                       |            |             |                   |                 |             |
| Found life less satisfying due to oral problems                             |            |             |                   |                 |             |
| Complete inability to function                                              |            |             |                   |                 |             |

### 10.3. Evaluation of safety

#### 10.3.1. Adverse events evaluation

- The severity of AE will be assessed in accordance with the MedDRA version 23.1.

## Version 2.6

- From the start of clinical trial drug administration to the end of administration, the occurrence and grade of adverse events are evaluated at each visit.
- The basic principles of grading are as follows

Grade 1: Side effects that are symptomatic but do not require treatment

Grade 2: Side effects that require treatment to alleviate symptoms but do not interfere with activities of daily living (ADL) and do not pose a threat to life

Grade 3: Side effects that can be life-threatening if left untreated

Grade 4: Life-threatening side effects

